**Primary outcome measures**					

Quality of life	EQ5D, SF36, INQOL	√	√	√	√

**Secondary outcome measures**					

Demographic statistics		√			

Severity of the disease	Rankin Scale	√			

Use of care resources and medicine	Client Service Receipt Inventory (CSRI)	√		√	√

Self efficacy	SE questionnaire from Schwarzer, SE NMD	√	√	√	√

Social support	SSLD (Sociale Steun Lijst-Discrepanties)	√	√	√	√

Satisfaction with relationship		√	√	√	√

Satisfaction with the appointment	QUality Of care Through the patient's Eyes (QUOTE)		√	√	√

Outcome measures for partners are listed in table 3. Among partners of patients, quality of life (EQ-5D) [24-27], self efficacy (SE questionnaire by Schwarzer, [29]), the need for social support (subscale emotional support of the Dutch questionnaire SSLD [30], satisfaction with the relationship (VAS scale and 1-10 reporting)[31], objective burden of care and satisfaction with and aspects of the visit (QUOTE questionnaire, [32])will be measured. Ojective burden of care is measured by asking after the amount of time a partner spends on caring for the partner and on doing household tasks in order to be able to relieve or support their partner with the chronic disease; time spent on delivering care for the chronically ill partner is the main predictor for the impact of the disease on the life of the partner [35].

**Table 3 T3:** Outcome measures and instrumentation partners

	Instruments	T0	T1	T2	T3
**Primary outcome measures**					

Quality of life	EQ5D	√	√	√	√

**Secondary outcome measures**					

Demographic statistics		√			

Self efficacy	SE questionnaire from Schwarzer	√	√	√	√

Social support	SSLD (Sociale Steun Lijst-Discrepanties)	√	√	√	√

Satisfaction with relationship		√	√	√	√

Satisfaction with the appointment	QUality Of care Through the patient's Eyes (QUOTE)		√	√	√

#### Economic evaluation

Cost effectiveness will be assessed from a societal perspective. Direct neuromuscular disease-related costs health care costs, including costs of outpatient care, physical-, speech- and occupational therapy, additional visits to other health care providers (GPs, specialist care, etc.), district nursing, receipt of aids and adaptations, prescription medication, professional home care and hospitalization will be included, as well as non-health care costs such as costs for paid and unpaid help. For unit cost prices, standard rates will be adopted from the national guideline [36] or real cost prices (e.g., for medication) will be obtained through the website of the Dutch Health Care Insurance Board (CVZ, http://www.medicijnkosten.nl). For shared medical appointments, a cost price will be calculated on the basis of available standard rates and real expenditures. The price year will be 2009, the currency Euros, and in view of the timescale of the study, costs and health benefits will not be discounted. Utilization of itemized resources over the trial period will be self-recorded by patients with a modified version of the Client Service Receipt Inventory (CSRI)[28]. Costs per patient will be calculated by multiplying resource volumes by unit costs.

Outcome measures will be obtained through standardized questionnaires, who patients and partners fill out at home at the start of the study period (T0), 1 week (T1), 3 months (T2) and 6 months after the intervention (T3). See Figure 1 and table 2 and 3. At the first measurements (T0) demographic data will be obtained.

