### Interventions

Care as usual: individual outpatient appointment.

Patients and partners who are randomized to the control group will have their regular control visit with one of the participating neuromuscular neurologists at the outpatient neurology department of the RUNMC. This one on one control visit substitutes the regular annual control visit the patients pay to the neurology department. The same items that are normally attended to during the control visit, are attended to by the neurologist. All physical examinations, prescriptions and referrals are conducted as deemed appropriate, and documented in the patient record. The regular one on one control visit takes 30 minutes.

Intervention: shared medical appointment

Patients and partners who are randomized to the intervention arm of the study will be invited to a shared medical appointment of 1,5 - 2 hours with one of the participating neuromuscular neurologists and a group mentor at the outpatient neurology department of the RUNMC. The same neurologists execute the individual appointments and the shared medical appointments. As well as for the individual appointments, the shared medical appointments substitute for the annual control visit of the patients. The same items the neurologist attends to in a one on one control visit are attended to during the shared medical appointment. The neurologist is supported by a group mentor, who facilitates the group process, fosters interaction between patients and manages time.

The group mentor starts with a short introduction in which the process of the shared medical appointment is explained and confidentiality is emphasized. Patients and their partners are asked to fill out a privacy form, which is kept in the patient's records, in order to emphasize the confidentiality of the group visit. If physical examinations are deemed necessary, they are conducted in a private examination room close to the group visit room directly after the shared medical appointment. Necessary prescriptions, referrals, and chart notes are being taken care of during or directly after the shared medical appointment. The neurologists have received training in conducting shared medical appointments prior to the study. The process of the shared medical appointments is described in appendix 1.

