#### Economic evaluation

An incremental cost-effectiveness analysis will be conducted from a societal perspective, relating differences in costs to difference in health outcome as measured by the Euroqol-5D, an instrument to evaluate different health states. Bootstrapping will be used for pair-wise comparisons in direct health care costs, direct non-health care costs, total direct costs, total indirect costs, and total costs between the two groups. Confidence intervals will be obtained by conventional re-sampling methods (bootstrapping). The cost effectiveness analysis will provide information on the marginal costs and effects of shared medical appointments relative to conventional one-to-one outpatient visits through the calculation of an incremental cost effectiveness ratio. Ratios will include the primary outcome of the trial, i.e., quality of life and two secondary outcome parameters; functional activities, and self-efficacy. Cost acceptability curves will be calculated showing the probability that the shared medical appointment is cost effective at specified ceiling ratios. In situations where there is no significant difference in effects, the use of cost-minimization analysis will be used for the reporting of cost differences only. Sensitivity analyses will be conducted, exploring the sensitivity of the conclusions to various sources of uncertainty, including sampling variation (e.g., differences in self-efficacy and functional abilities in both groups) and point-estimates (e.g., unit cost prices of major cost drivers).

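### The societal analysis will compare total indirect costs, but the article names no item for that category and no patient or partner visit time, which differs between the arms by design.

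*Protocol article*

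**What the plan says.** Under Outcomes, Economic evaluation, the article states: "Cost effectiveness will be assessed from a societal perspective". It lists disease-related health care items, which "will be included, as well as non-health care costs such as costs for paid and unpaid help". On the price of the intervention it says: "For shared medical appointments, a cost price will be calculated on the basis of available standard rates and real expenditures". Patients report their own resource use on a modified service-use inventory (CSRI), which Table 2 schedules at T0, T2 and T3. The Outcomes section describes this outcome as services, medication, compliance with medication and help with daily activities. From partners, the time collected is time spent on care and household tasks.

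Under Statistical analysis, Economic evaluation, the planned bootstrap comparisons cover "direct health care costs, direct non-health care costs, total direct costs, total indirect costs, and total costs between the two groups". If effects do not differ significantly, a cost-minimization analysis reports cost differences only.

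Under Interventions, patients and partners in the group arm "will be invited to a shared medical appointment of 1,5 - 2 hours". For the control arm the text says: "The regular one on one control visit takes 30 minutes".

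**The concern.** Two parts of the same article do not match. The analysis section has a line for indirect costs, separate from direct health care and direct non-health care costs. The section that sets out what is costed, and the descriptions of the data collected, name nothing that clearly belongs on that line.

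The gap matters because one unnamed item is tied to the intervention itself. A group visit uses less neurologist time per patient and more time from each patient and partner. A price built from standard rates and expenditures captures the provider's side of that exchange, and nothing named captures the attenders' side. Under a societal perspective both sides count.

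The stakes are highest under the cost-minimization fallback, where the cost difference alone becomes the economic result. The Discussion also presents efficient use of time as a central reason for the trial.

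**Working it through.** The article states no cost result or time balance that could be reproduced, so the check uses its visit figures directly.

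**Step 1. Match cost categories to named items.**

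- Direct health care costs: outpatient care, therapies, other providers, nursing, aids, medication, home care and hospital stays are named.
- Direct non-health care costs: paid and unpaid help are named.
- Total indirect costs: no item is named. Lost work, travel and time at the visit do not appear in the cost list, in the Outcomes description of resource use or in the partner measures.

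**Step 2. Inputs.**

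- Control visit: 30 min (Interventions).
- Group visit: D = 90 to 120 min (Interventions; What is a shared medical appointment?).
- Group size: g = 6 to 10 patients, with one physician and one mentor (What is a shared medical appointment?).
- Partners are invited in both arms (Interventions), where applicable (Analysis of outcome measures).
- One group visit per patient in the study (Discussion).

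**Step 3. Formulas, in minutes per patient.**

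- Extra time per attender = D − 30; for a couple, 2 × (D − 30).
- Neurologist time in the group arm = D / g; saving = 30 − D / g.
- Mentor time added = D / g.
- Net staff change = 2 × D / g − 30.
- Ratio = extra attender time / neurologist time saved.

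**Step 4. Results.**

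| D | g | Neurologist saving | Mentor added | Net staff change | Extra per attender | Ratio, patient alone | Ratio, couple |
|---|---|---|---|---|---|---|---|
| 90 | 6 | 15 | 15 | 0 | 60 | 4.0 | 8.0 |
| 90 | 8 | 18.75 | 11.25 | −7.5 | 60 | 3.2 | 6.4 |
| 90 | 10 | 21 | 9 | −12 | 60 | 2.9 | 5.7 |
| 120 | 6 | 10 | 20 | +10 | 90 | 9.0 | 18.0 |
| 120 | 8 | 15 | 15 | 0 | 90 | 6.0 | 12.0 |
| 120 | 10 | 18 | 12 | −6 | 90 | 5.0 | 10.0 |

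At every combination, extra attender time exceeds both the neurologist saving and the mentor addition. Net staff time runs from 12 min saved to 10 min added per patient. These are scheduled minutes. Examinations and record-keeping after the group session are not included.

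**Step 5. Money, by assumption only.** The article gives no value of time. At an assumed EUR 5 to 30 per hour, one attender's extra time is worth 1 × 5 = EUR 5 to 1.5 × 30 = EUR 45. For a couple this is EUR 10 to 90. The range is illustrative, and the article gives no total cost or cost variance to set it against.

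**The case against.** The strongest reply is that the list is illustrative. Non-health care costs are introduced by example, the modified inventory is not shown, and a journal article may leave the full item list to a longer protocol. A planned indirect-cost comparison even suggests that such costs were intended. This stands as a limit: the items are not named, and the article does not show that they will be left out. It does not remove the mismatch, because the article sets out both the cost list and the comparison.

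Unpaid help is sometimes classed as an indirect cost. Here it is called a non-health care cost, and the analysis has a separate direct non-health care line. Reclassifying it would still not bring in visit time.

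Four stronger readings are tempting, and the article does not support them:

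- **That only the neurologist's side is costed.** The list covers many services and unpaid help, and the price of the group visit can include the mentor.
- **That visit time is the largest time difference between the arms.** This holds for scheduled visit time only. No figures are given for six-month differences in informal care or work absence.
- **That the ratio of 6 to 18 applies to every patient.** It assumes that a partner attends. For a patient alone it is about 3 to 9. It also compares minutes that carry different prices, so it is not a ratio of costs.
- **That the whole incremental cost is biased in a known direction.** The direction is known for visit time. For lost work it is unknown, and travel should largely cancel because each arm has one visit to the same department.

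**Conclusion.** The point holds in a limited form. The planned comparison of total indirect costs has no named content or data source, and patient and partner visit time is not named although the perspective is societal. If costs are computed from the named items only, 60 to 90 minutes per attender (120 to 180 per couple) go uncounted, all in the group arm, and the visit-related incremental cost is biased in favour of the group visit.

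This rests on the stated visit lengths and group sizes being met, on partners attending equally in the two arms where present, and on time having a positive value. The effect in euros cannot be derived from the article. The point concerns the economic evaluation and leaves the primary quality-of-life analysis untouched. It deserves a change because valuing visit time removes a one-directional error at little cost.

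**What to change.** - Add patient visit time, and partner visit time where a partner attends, to the cost list in both arms. Value it from scheduled or recorded visit length, using a time value from the national costing guideline if it gives one, and state the value used.
- Name the items that make up total indirect costs and the instrument that records each.
- If no lost-work data are collected, drop the indirect-cost category and narrow the stated perspective to health care plus informal care. With results expected in 2012, new questionnaire items may come too late, so this fallback matters.

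The cost is modest. Scheduled visit lengths are already known. Partner attendance has to be known or assumed, with a sensitivity analysis if it is assumed. There is a little more analysis work, and the cost difference will be somewhat less favourable to the group visit than one that leaves visit time out.

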### Statistical analysis

#### Sample size

On the basis of the literature [37,38] group visits may be expected to lead to a clinically relevant improvement in quality of life of 5 points on the total SF-36 score. Assuming a standard deviation of 12 [39], 92 patients need to be enrolled in both groups to achieve a statistical power of 80% (alpha = 0.05, two-sided). Taking into account non-evaluable patients, to adjust for imbalances and to be able to do subgroup analysis on age, sex, gender and severity, 135 patients will be enrolled in both groups. In order to be able to evaluate 270 patients, the aim is to include 300 patients.

#### Analysis of outcome measures

300 neuromuscular patients and if applicable their partners will be included in the study. The primary analysis will be an intention-to-treat analysis on the area under the curve of the quality of life scores (average response during 6 months). A linear mixed model will be used with random factor group and fixed factors treatment, baseline score and type of neuromuscular disease. Other outcome parameters will be evaluated in a similar way and additional per protocol analyses will be carried out.

For the analyses SPSS version 17 statistical software will be used. A p-value of 0.05 will be considered statistically significant. Missing data will be imputed using multiple imputation techniques.

#### Economic evaluation

An incremental cost-effectiveness analysis will be conducted from a societal perspective, relating differences in costs to difference in health outcome as measured by the Euroqol-5D, an instrument to evaluate different health states. Bootstrapping will be used for pair-wise comparisons in direct health care costs, direct non-health care costs, total direct costs, total indirect costs, and total costs between the two groups. Confidence intervals will be obtained by conventional re-sampling methods (bootstrapping). The cost effectiveness analysis will provide information on the marginal costs and effects of shared medical appointments relative to conventional one-to-one outpatient visits through the calculation of an incremental cost effectiveness ratio. Ratios will include the primary outcome of the trial, i.e., quality of life and two secondary outcome parameters; functional activities, and self-efficacy. Cost acceptability curves will be calculated showing the probability that the shared medical appointment is cost effective at specified ceiling ratios. In situations where there is no significant difference in effects, the use of cost-minimization analysis will be used for the reporting of cost differences only. Sensitivity analyses will be conducted, exploring the sensitivity of the conclusions to various sources of uncertainty, including sampling variation (e.g., differences in self-efficacy and functional abilities in both groups) and point-estimates (e.g., unit cost prices of major cost drivers).

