### Randomization and blinding

Concealed randomization will be performed through computer-generated randomization software. Every included patient will be randomly allocated to one of the two study arms by the computer. The method of simple randomization is applied. In view of the nature of the interventions, blinding of the participants, participating neurologists and primary researcher is not possible. The statistician who conducts the analysis of the data will, however, be blinded for the patients' groups.

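### The cost comparison names no baseline term although resource use is collected at T0, and the source of the EQ-5D effect in the ratio is left open

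*Protocol article*

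**What the plan says.** Under Statistical analysis, Economic evaluation, the protocol article gives costs their own method: "Bootstrapping will be used for pair-wise comparisons in direct health care costs", followed by direct non-health-care, total direct, total indirect and total costs, each compared between the two arms. Intervals come from bootstrapping. The section then forms incremental cost-effectiveness ratios and acceptability curves. If effects do not differ significantly, it falls back on cost-minimization, which reports cost differences only. It names no baseline covariate, and its listed sensitivity analyses include no baseline adjustment.

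Table 2 schedules "Use of care resources and medicine" (the CSRI) at T0, T2 and T3, and EQ-5D at T0 to T3. The other Economic evaluation section, under Outcomes, computes cost per patient as volumes times unit costs.

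Under Analysis of outcome measures, the clinical model for quality of life has "fixed factors treatment, baseline score and type of neuromuscular disease", plus a random factor for group. That section adds that the remaining outcomes are analysed along the same lines.

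Under Randomization and blinding: "The method of simple randomization is applied".

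**The concern.** The baseline is collected for both cost and utility and is used in the clinical model, but the stated cost comparison has no place for it. On its ordinary reading, a pair-wise comparison between two arms is a two-sample contrast. Simple randomization does nothing to balance prior care use across the nine diagnosis groups, so any chance difference at T0 is left to the analysis.

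Two things are at stake. The first is precision: if care use before the visit predicts care use after it, the interval for incremental cost is wider than it needs to be. The second is consistency within the ratio: an adjusted EQ-5D effect from the clinical model could end up paired with an unadjusted cost difference.

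The cost side could carry the whole economic conclusion. The Discussion notes that each patient gets one appointment and six months of follow-up, so a non-significant effect is a real possibility. The cost-minimization rule would then apply.

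**Working it through.** **The plan's own figures.** Inputs from Sample size: "improvement in quality of life of 5 points on the total SF-36 score"; "Assuming a standard deviation of 12"; "92 patients need to be enrolled in both groups to achieve a statistical power of 80% (alpha = 0.05, two-sided").

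- Normal approximation: n = 2 × (1.960 + 0.842)² × (12/5)² = 2 × 7.849 × 5.76 = 90.4, so 91 per arm.
- The t-test version gives 91.4, so 92 per arm. The stated figure is reproduced.
- 270 / 0.90 = 300, which matches the inclusion target at 10% loss.

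Nothing here disputes these figures. They concern the SF-36; the article gives no SD or target difference for costs or EQ-5D.

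**Inputs for this point.**

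- Arm size: "135 patients will be enrolled in both groups", so n = 135.
- Correlation r between T0 and follow-up cost: not given. Assumed range 0.3 to 0.8.

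**Formulas** (two arms of equal size, linear adjustment, in SD units).

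- Standard error of the chance baseline difference: √(2/n) = √(2/135) = 0.122 SD. The 95% range is ±1.96 × 0.122 = ±0.24 SD.
- Part of a baseline difference that stays in the unadjusted follow-up difference: r times that difference.
- Adjusted over unadjusted standard error: √(1 − r²).

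| Assumed r | Carry-over from a 1-SE imbalance (SD) | 95% range of carry-over (SD) | SE ratio | SE reduction |
|---|---|---|---|---|
| 0.3 | 0.037 | ±0.07 | 0.954 | about 5% |
| 0.5 | 0.061 | ±0.12 | 0.866 | 13% |
| 0.7 | 0.085 | ±0.17 | 0.714 | 29% |
| 0.8 | 0.097 | ±0.19 | 0.600 | 40% |

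**The text side by side.**

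- *Costs.* The clinical section extends its approach to the other outcomes, and resource use is a listed secondary outcome. The economic section then gives costs, built from the same CSRI data, a method of their own with no covariate. Read together, they leave unclear whether the T0 CSRI enters the cost comparison.
- *EQ-5D.* It is one of the primary quality-of-life measures, so the clinical model yields a baseline-adjusted EQ-5D effect. The economic section says that the ratios include the primary outcome, but not whether they use that model's estimate or a difference of arm means.

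**The case against.** The strongest reply is that this is a condensed article and its economic section never calls the comparison raw or unadjusted. Bootstrapping is a way to obtain intervals and can resample adjusted estimates, so covariates could sit in a fuller plan. The clinical section's extension to other outcomes also covers resource use on its face, so the T0 CSRI is not without any stated role. This stands as far as it goes: a reader might infer that the plan ignores its baselines, but the text does not say so. It does not dispose of the point, because the article does not leave the cost method open. It states one, distinct from the clinical model and without a baseline term.

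A reader might also infer that a chance EQ-5D difference at T0 would count as health gain in the ratio. The document does not support that. The bootstrap sentence lists cost categories only, and the clinical model already adjusts EQ-5D for baseline. What remains is that the link between that estimate and the ratio is not stated.

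A third inference would be that the result is biased, or that imbalance passes in full into the estimate. Neither follows. Under randomization the unadjusted contrast is unbiased, its bootstrap interval reflects chance imbalance, and only about r times the imbalance carries over.

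Finally, the size should not be set against the 5/12 SD effect used for sample size. That is an SF-36 figure and does not measure distortion of costs or of the ratio. The article also gives no data on how far care use differs between the diagnosis groups.

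**Conclusion.** The point holds mainly for costs, as a matter of precision and of chance imbalance in the one trial actually run. It is not a finding of bias or of an invalid analysis. With 135 per arm, the standard error of a baseline difference is 0.122 SD. Leaving the baseline out forgoes a reduction in the standard error of the cost difference of about 5% to 40%, or 13% to 29% if r is 0.5 to 0.7. All of these percentages rest on assumed correlations, equal arms and linear adjustment.

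For EQ-5D the point is narrower: the economic section should say which estimate enters the ratio.

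The change is worth making because the T0 data are already scheduled, and because the cost-minimization rule would make the cost difference the sole basis of the economic conclusion.

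**What to change.** In Statistical analysis, Economic evaluation:

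- Estimate incremental cost by regression on arm, T0 CSRI cost and disease type.
- Take the incremental EQ-5D effect from a model with T0 EQ-5D and disease type, in line with Analysis of outcome measures, and say so.
- Refit both models within each bootstrap sample, so that the ratio and the acceptability curve use adjusted differences.
- Use the same adjusted cost difference if the cost-minimization rule applies.
- Keep the unadjusted comparison as a sensitivity analysis.

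The cost is a few sentences and slightly more programming. No new data are needed, since both baselines are in the T0 questionnaires, and the sample size does not change.

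### The economic bootstrap takes no account of the visit groups that the primary model allows for, so cost and cost-effectiveness intervals will be too narrow if patients in a group are alike

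*Protocol article*

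**What the plan says.** Patients are randomized individually (Randomization and blinding). In the intervention arm 6-10 patients are seen together in one session; control patients have a one-to-one visit (What is a shared medical appointment?; Interventions). Each patient attends one session during the study (Discussion).

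For quality of life, Analysis of outcome measures states: "A linear mixed model will be used with random factor group and fixed factors treatment, baseline score and type of neuromuscular disease". Other outcomes are to be handled similarly.

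The Economic evaluation under Statistical analysis sets its own method. Costs are compared between arms by bootstrapping, and "Confidence intervals will be obtained by conventional re-sampling methods (bootstrapping" is the whole specification of the intervals. Incremental ratios and acceptability curves follow, with the EQ-5D as the main health effect. No resampling unit is given and the visit groups are not mentioned.

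On the price of the intervention, the Economic evaluation under Outcomes states: "For shared medical appointments, a cost price will be calculated on the basis of available standard rates and real expenditures".

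**The concern.** The two analyses treat the same patients differently. The EQ-5D is one of the primary quality-of-life instruments, so it is analysed with a group effect in the clinical model. It is also the effect side of the cost-effectiveness ratio, where ordinary resampling would treat each patient as independent.

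Patients in a session share a neurologist, a mentor and a discussion, and the trial's rationale is that they influence one another. Positive correlation within sessions is therefore plausible for quality of life, and possible for later use of care. A bootstrap that draws single patients breaks up the sessions and loses the between-session variation. The intervals would then be too short, and the acceptability curves would look more certain than the data allow. Cost-effectiveness is a headline aim of this trial.

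**Working it through.** **Inputs from the article.** Effect "clinically relevant improvement in quality of life of 5 points on the total SF-36 score"; "Assuming a standard deviation of 12"; "92 patients need to be enrolled in both groups to achieve a statistical power of 80% (alpha = 0.05, two-sided"; "135 patients will be enrolled in both groups"; group size m = 6 to 10. For 135 patients this gives 135/10 = 13.5, about 14 groups, to 135/6 = 22.5, about 23 groups.

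**Assumed, because the article does not give it.** ICC of 0.01 to 0.10. The total variance is taken as equal in the two arms.

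**The plan's own figure.** n = 2 × (1.96 + 0.8416)² × 12² / 5² = 90.4, or 91 per arm by the normal formula. The exact t calculation gives 80.3% power at 92 and 79.8% at 91, so 92 per arm reproduces. It assumes independent patients.

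**Standard error with grouping in one arm.** Var(difference) = SD² × (DE/n₁ + 1/n₀), with DE = 1 + (m − 1) × ICC. Ordinary resampling corresponds to DE = 1. With equal arms:

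- true SE / naive SE = √((1 + DE)/2)
- actual two-sided error of a nominal 5% test = 2 × [1 − Φ(1.96/ratio)]

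Example, m = 8 and ICC 0.05: DE = 1 + 7 × 0.05 = 1.35; ratio = √(2.35/2) = 1.084; error = 2 × [1 − Φ(1.808)] = 7.1%.

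| ICC | SE ratio, m = 6 / 8 / 10 | Two-sided error, m = 6 / 8 / 10 |
|---|---|---|
| 0.01 | 1.012 / 1.017 / 1.022 | 5.3% / 5.4% / 5.5% |
| 0.02 | 1.025 / 1.034 / 1.044 | 5.6% / 5.8% / 6.1% |
| 0.05 | 1.061 / 1.084 / 1.107 | 6.5% / 7.1% / 7.7% |
| 0.10 | 1.118 / 1.162 / 1.204 | 8.0% / 9.2% / 10.4% |

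The naive SE is therefore too small by 1 − 1/1.012 = 1.2% at one end and 1 − 1/1.204 = 16.9% at the other.

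**Simulated coverage of a nominal 95% percentile bootstrap interval.** Normal data, 3,000 trials per setting, 135 controls. The Monte Carlo SE is about 0.4 to 0.6 percentage points.

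| Groups × size | ICC | Single patients resampled | Whole groups resampled |
|---|---|---|---|
| 14 × 10 | 0.01 | 94.0% | 93.9% |
| 14 × 10 | 0.05 | 91.2% | 92.3% |
| 14 × 10 | 0.10 | 88.5% | 93.0% |
| 17 × 8 | 0.01 | 93.7% | 94.1% |
| 17 × 8 | 0.05 | 92.7% | 93.4% |
| 17 × 8 | 0.10 | 89.6% | 92.7% |
| 23 × 6 | 0.01 | 94.7% | 94.4% |
| 23 × 6 | 0.05 | 92.9% | 93.9% |
| 23 × 6 | 0.10 | 91.5% | 94.1% |

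At ICC 0.01 the two methods cannot be told apart. At 0.05 the gain is about one point. At 0.10 it is about 3 to 4.5 points. The group bootstrap itself stays slightly below 95%, because it rests on few groups. Skewed costs were not simulated.

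**Sample size.** With the grouping allowed for, 80% power for 5 points needs 93 to 132 per arm over the same range, within the planned 135. In the worst case (m = 10, ICC 0.10), SE = 12 × √((1.9 + 1)/135) = 1.759 and power = Φ(5/1.759 − 1.96) = 81%.

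**The case against.** The article does not say that single patients are resampled, and an article may leave the resampling unit to a fuller plan. That is fair, and it makes the point conditional. The article does, however, describe the method as conventional, and it does so directly after a clinical model that names the group. An analyst following the text would resample patients.

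The effect also depends on an ICC that nobody has stated. Many cost items, such as medication, home care and hospitalization, are individual use and may correlate little within a session. This stands: at ICC 0.01 to 0.02 the effect is small.

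Two stronger readings are tempting, and the article supports neither.

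- A reader might infer that the primary model is also wrong, because controls belong to no visit group. The article does not say how controls are coded, and that detail is commonly left to the full plan. In simulation (17 groups of 8 against 136 controls), giving each control its own level kept the type I error at 4.7% to 5.6% for ICCs from 0 to 0.10. Coding all controls as one group would distort the result (an approximate calculation gives a conservative 2.1% to 3.6%), but nothing in the text says or implies that coding.
- A reader might infer that session cost is shared by everyone in a session and so is fully clustered. The article speaks of one cost price, and patient costs are volumes times unit costs. The natural reading is a single unit price. As each patient attends one session, that price is the same for all attenders and adds no between-session variance.

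**Conclusion.** The point holds for the economic evaluation only. The protocol allows for visit groups in its clinical model and leaves them out of the stated bootstrap. If patients are resampled singly, cost and cost-effectiveness intervals and acceptability curves will be too narrow whenever the within-group correlation is positive. The SE is understated by a factor of 1.01 to 1.20, and the two-sided error is 5.3% to 10.4%. This rests on an assumed ICC of 0.01 to 0.10, groups of 6-10, equal arms and equal variances. The consequence is negligible at the low end and worth correcting at the high end. It does not show that the primary model's standard errors are wrong or that the trial is underpowered.

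**What to change.** In the Economic evaluation under Statistical analysis, state that the bootstrap is done within arm: whole visit groups are drawn with replacement in the intervention arm, and single patients in the control arm. Keep each patient's cost and effect together in every draw, and use the same replicates for the intervals and the acceptability curves. Say how intervention patients who attended no session enter, for example as units of one. Because there will be only about 14 to 23 groups, consider a small-sample correction.

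As a minor clarification to Analysis of outcome measures, state that group means the visit group and that each control is its own level.

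The cost is a few sentences, some analysis code and a record of which session each patient attended. Intervals become slightly wider, and coverage may still be a little under 95%. Recruitment and trial conduct do not change.
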